#### Inclusion criteria

To enroll in the trial, subjects must: 1) be aged 18–65 years; 2) be scheduled to undergo elective laparoscopic surgery under general anesthesia; 3) have no experience with intradermal needling therapy; 4) not be enrolled in any other clinical trials; 5) have no cognitive dysfunction, aphasia, mental illness, or other communication barriers; and 6) be able to sign an informed consent form.

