*Psychological status:* We will use the Hospital Anxiety and Depression Scale (HADS) to evaluate the subjects’ psychological status [23]. HADS has 14 items, of which seven evaluate depression and seven evaluate anxiety. To determine the severity of each condition, the depression and anxiety subscale scores are divided into categories of 0–7 points (asymptomatic), 8–10 points (symptoms suspected), and 11–21 points (symptoms indicated). The first assessment will be performed 6 h after laparoscopic surgery. Another HADS assessment will be performed on the day of discharge from the hospital.

*Quality of life:* We will use the Gastrointestinal Quality of Life Index (GIQLI) to evaluate the subjects’ quality of life [24]. The GIQLI was specifically designed to evaluate quality of life in subjects with gastrointestinal syndromes. It includes five aspects: subjective symptoms, physiological functions, daily life, social activities, and psychological/emotional state. There are 36 items in total, each adding 0–4 points to the score. Thus, the highest possible score is 144 points; higher scores indicate better quality of life. A normal score is in the range 121–125. The GIQLI will be evaluated three times. The first assessment will occur 6 h after the laparoscopic surgery; the second will occur on the day of discharge from the hospital, and the third will occur 1 month after discharge from the hospital.

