#### Statistical analysis

##### Analysis procedures

*Sample distribution:* We will describe the size and dropout rate of each dataset. Detailed reasons for any dropouts will be provided.

*Balanced comparison:* We will compare the general subject data and then evaluate comparability between the two groups.

*Efficacy analysis:* We will use the time until the first postoperative flatus as a primary outcome to assess the efficacy of XNKQAT by intradermal needling in the treatment of gastrointestinal dysfunction after laparoscopic surgery. We will calculate the average and standard deviation to describe the outcome and use an independent-samples *t* test to compare the two groups. Eight secondary outcomes (time until first postoperative defecation; level of abdominal pain, abdominal distension, and nausea; blood ghrelin level; vomiting; psychological status; and quality of life) will be compared between the two groups to determine the efficacy of XNKQAT intradermal needling. The mean and standard deviations of these parameters will be reported. To record the subjects’ psychological status, we will record their scores and determine their classification based on the standards mentioned above. To determine the time until the first postoperative defecation, we will use the same method as the time until the first postoperative flatus. To analyze abdominal pain, abdominal distension, nausea, vomiting, ghrelin level, and quality of life, we will use repeated measures analysis of variance (RMANOVA). Before RMANOVA, we will carry out a test of sphericity to ensure that the data are suitable for this method. If the data do not meet spherical symmetry requirements, we will use the ε correction factor to correct the degrees of freedom before applying RMANOVA. The Mann–Whitney *U* test or Spearman’s Rank correlation coefficient tests will be used to analyze the categorization standards for psychological status.

*Safety analysis:* According to the definition of adverse events, specific adverse events will be listed, along with their severity level, causes, and explanations. The number of adverse events, and the adverse event rate, will be described statistically. If they need to be compared between groups, the χ^2^ test or Fisher’s exact test will be used.

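### The only between-group test named for HADS uses three severity bands rather than the recorded 0–21 scores, which costs power at 14 to 17 per arm

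*Protocol article*

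**What the plan says.** Under Secondary outcomes, the article describes HADS as two seven-item subscales, each split into 0–7, 8–10 and 11–21 points. The first assessment is 6 h after surgery, and "Another HADS assessment will be performed on the day of discharge from the hospital".

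Under Analysis procedures (Efficacy analysis), eight secondary outcomes are to be compared between the groups, psychological status among them. The text then assigns methods:

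- All eight: "The mean and standard deviations of these parameters will be reported".
- Defecation time: the same method as flatus time, a t test.
- Six others: "To analyze abdominal pain, abdominal distension, nausea, vomiting, ghrelin level, and quality of life, we will use repeated measures analysis of variance". Psychological status is not on this list.
- Psychological status: "we will record their scores and determine their classification based on the standards mentioned above". Mann–Whitney U or Spearman rank correlation "tests will be used to analyze the categorization standards for psychological status".

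Statistical analysis methods adds two general rules. Quantitative variables measured repeatedly go to repeated measures ANOVA; qualitative data go to Mann–Whitney or Spearman.

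**The concern.** HADS is the one multi-item scale whose named test works on categories. GIQLI, the other questionnaire, is analysed as a score, and no reason is given for the difference. On the bands, a fall from 7 to 2 points is no change, while a fall from 8 to 7 is a full category. The more subjects there are in the 0–7 band, the less the test can see.

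Spearman's coefficient is offered as an alternative for the same comparison. It measures association and gives no between-arm difference on the HADS scale.

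At stake is the reading of one secondary outcome: a non-significant band test could be reported as no effect on anxiety or depression when the recorded scores might have shown one.

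**Working it through.** **1. Sample size available.** The article's Sample size estimation section gives SDs of 2.89 and 4.31 h, a difference of 4 h, and Z values of 1.96 and 0.84.

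n = (1.96 + 0.84)² × (2.89² + 4.31²) / 4² = 7.84 × 26.9282 / 16 = 13.19, so 14 per group. With 15% loss, 14 / 0.85 = 16.5, so 17 per group and 34 in total.

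The stated figures reproduce. They concern flatus time only; nothing is sized for HADS.

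**2. What a band test needs, with no distribution assumed.** Take the most favourable pattern: no acupuncture subject is above the lowest band, and k sham subjects are in one higher band. With n per arm, the tie-corrected Mann–Whitney statistic (no continuity correction) reduces to z = √[(2n − 1)k / (2n − k)].

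- n = 14, k = 3: √(27 × 3 / 25) = 1.80, p = 0.072. k = 4: √(27 × 4 / 24) = 2.12, p = 0.034.
- n = 17, k = 3: √(33 × 3 / 31) = 1.79, p = 0.074. k = 4: √(33 × 4 / 30) = 2.10, p = 0.036.

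So at least 4 sham subjects must be above the lowest band even when no treated subject is. By Fisher's exact test it takes 5 (p = 0.041 and 0.044).

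**3. Power on bands and on scores, by simulation.** One subscale at one time point, two-sided α = 0.05, 2,000 runs per case. Assumed, because the documents give no HADS figures: gamma-shaped scores rounded and clipped to 0–21, SD 3.5 in both arms, true difference 2 or 3 points. Bands are tested by Mann–Whitney, scores by Welch t. Paired entries are 14 / 17 per arm.

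| Sham mean | Sham arm in 0–7 | Bands, diff 2 | Scores, diff 2 | Bands, diff 3 | Scores, diff 3 |
|---|---|---|---|---|---|
| 4 | 86% | 4 / 7% | 39 / 46% | 7 / 12% | 74 / 78% |
| 5 | 80% | 8 / 10% | 37 / 41% | 13 / 17% | 65 / 73% |
| 6 | 72% | 12 / 16% | 34 / 40% | 20 / 24% | 63 / 70% |
| 7 | 62% | 17 / 19% | 32 / 37% | 28 / 36% | 60 / 69% |
| 9 | 37% | 27 / 30% | 33 / 38% | 45 / 53% | 59 / 68% |

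**4. Sensitivity to the assumed shape.** Holding the SD fixed while the treated mean falls gives the treated arm a long upper tail, which depresses band power. At 17 per arm with sham mean 6, SD 3.5 and a 3-point difference, band power rises from 24% to about 40% with rounded normal scores, and to about 58% if the SD shrinks in proportion to the mean. Mann–Whitney power on the scores falls from about 87% to 65% under the normal shape. Banding lost power in every case tried, but the size of the loss moves a good deal.

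**The case against.** The strongest reply is that the article does not exclude an analysis of the scores. It promises means and SDs for all secondary outcomes, says that scores as well as classes are recorded, and has a general rule sending repeated quantitative data to repeated measures ANOVA. HADS scores are quantitative and measured twice. This stands in part: a reader might infer that the scores will never be compared, and the text does not go that far. But the general rule does not name HADS, the specific list omits it, and the pair of methods given to HADS is the pair reserved for qualitative data. If the rule does apply, HADS has two analyses and no stated precedence.

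A reader might also infer from the entry criterion that subjects must "have no cognitive dysfunction, aphasia, mental illness, or other communication barriers" that most will sit in the 0–7 band, so that the outcome can hardly show a difference. The documents do not support that as fact. The criterion sets no HADS ceiling, it sits among communication barriers, and the first HADS is taken 6 h after surgery. No distribution is given.

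Nor would a null result be attributable to banding alone. With the SD fixed at 3.5, Welch t power on the scores is below 80% in every row above, so the small sample contributes too. Finally, the bands are a recognised clinical summary, the scores are not lost, and this is one of eight secondary outcomes. All of that stands and limits the weight of the point.

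**Conclusion.** The point holds in conditional form. The one test the protocol names for HADS discards information that the trial already records. The loss is severe if about 70% or more of the sham arm scores 0–7 (bands 4–24%, scores 34–78%) and moderate in a more symptomatic group (sham mean 9: 27–53% against 33–68%). These figures rest on the assumed gamma shape, SD 3.5 and differences of 2 or 3 points; other shapes raise band power. The count of 4 (or 5) sham subjects needed in the best case rests on no assumed distribution. The objection to Spearman's coefficient as a group comparison needs no figures. The primary conclusion on flatus time is unaffected.

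**What to change.** In Analysis procedures, state that each HADS subscale score at discharge is compared between arms, adjusted for the 6 h score, with the estimated difference and 95% CI. State also that the 6 h HADS precedes the first treatment: the Intervention section places the first evaluation there, but the HADS paragraph gives only the time. Keep the three bands as a descriptive table by arm and visit. Remove Spearman's correlation as a group comparison.

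The cost is about two sentences and no new data. The small downside is that the banded clinical summary becomes descriptive only.

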#### Statistical analysis methods

The data will be analyzed according to the intention-to-treat (ITT) principle; that is, all subjects who are initially included in one of the two groups will be considered in the analysis. The analysis of efficacy and safety indicators will be carried out per-protocol (PP) and will include all subjects who complete the whole trial process. The quantitative variables of the research data will be statistically described using $$ \overline{\mathrm{X}}\kern0.5em \pm \kern0.5em \mathrm{SD} $$. A record of qualitative variables will be kept using the number of cases in each category. To compare quantitative variables, if the data come from repeated measurements, the RMANOVA method will be used, and sphericity testing will be used beforehand to determine whether a correction is needed. Qualitative data will be analyzed using the Mann–Whitney *U* test or Spearman’s rank correlation. The χ^2^ test or Fisher’s exact test will be used to compare the occurrence rates of countable data. Statistical testing will be two-tailed, with *P* values < 0.05 considered significant. SPSS 19.0 software will be used for all statistical calculations.

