#### Elimination criteria

Subjects will be eliminated from the trial if: 1) their laparoscopic surgery is changed to laparotomy; 2) they refuse to undergo the treatment for any reason; 3) serious syndromes, such as biliary fistula or peritonitis, arise during the treatment; 4) they transfer to another specialist for treatment; 5) they become comatose or die; 6) they are unable to attend the follow-ups for any reason; 7) they do not match the inclusion criteria and were accidentally included; and 8) they do not comply with the treatment or fail to provide information that may be important in the evaluation.

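### Intention-to-treat is promised, but the next sentence assigns efficacy and safety to per-protocol completers; no primary set is named, and the elimination rules make the completer set a selected one

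*Protocol article*

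**What the plan says.** Two consecutive sentences under Statistical analysis methods in the protocol article set the analysis population. The first invokes intention-to-treat, under which "all subjects who are initially included in one of the two groups will be considered in the analysis". The second reads: "The analysis of efficacy and safety indicators will be carried out per-protocol (PP) and will include all subjects who complete the whole trial process". Nothing says which set is primary, or that each outcome will be analysed in both.

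The Elimination criteria section lists who leaves the trial. Among the reasons are that "they refuse to undergo the treatment for any reason", that "serious syndromes, such as biliary fistula or peritonitis, arise during the treatment", that "they become comatose or die", that "they are unable to attend the follow-ups for any reason", and that "they do not comply with the treatment or fail to provide information that may be important in the evaluation". Transfer to another specialist is a further reason.

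Follow-up extends well past the primary outcome. For the quality-of-life index, "the third will occur 1 month after discharge from the hospital". The pilot mean times to first flatus (Background) were 15.21 h and 28.32 h.

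**The concern.** The Analysis procedures section contains an efficacy analysis and a safety analysis and no other outcome analysis. If both are per-protocol, intention-to-treat governs no outcome. If both populations are meant, nobody has said which one carries the primary t test, and the choice could be made after the results are seen.

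The completer set is also not a neutral subset. Several elimination reasons arise after allocation and are plausibly linked to gut recovery or to harm. Three things are at stake:

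- **Lost primary data.** A subject whose flatus time was recorded within days may be dropped for an event weeks later.
- **Bias.** Excluding subjects for reasons related to outcome or treatment breaks the comparison that randomisation protects.
- **Safety.** Subjects who die, become comatose, develop peritonitis or refuse further treatment are eliminated by rule. They are therefore missing from the population in which harms are compared.

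**Working it through.** **1. Whether the sentences can be reconciled.** Sentence one covers the data and everyone initially included. Sentence two covers efficacy and safety and only those who finish. The second takes in every outcome analysis that the Analysis procedures section describes. The text offers no rule for putting the two together.

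**2. The plan's own sample size.** Inputs from Sample size estimation: Z values 1.96 and 0.84, SDs 2.89 h and 4.31 h, difference 4 h, loss 15%.

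- n = (1.96 + 0.84)² × (2.89² + 4.31²) / 4² = 13.19, rounded up to 14 per group.
- 14 / (1 − 0.15) = 16.5, rounded up to 17 per group, 34 in total.

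This reproduces the stated figures. The plan therefore expects about 0.15 × 17 = 2.55, or 3 subjects per arm, to be lost.

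**3. Worst-case shift in one arm's mean.** Assumptions (mine): normal flatus times, 17 per arm, and the 3 lost subjects are the slowest in that arm, with no offsetting loss in the other.

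- The expected values of the three largest of 17 standard normal observations are 1.029, 1.319 and 1.794, which sum to 4.142.
- All 17 expectations sum to zero, so the other 14 average −4.142 / 14 = −0.296 SD. A simulation of 200,000 samples gave −0.294 SD.
- Slowest three lost from the acupuncture arm (SD 2.89): 0.294 × 2.89 = 0.85 h faster, 0.85 / 4 = 21% of the target, **in favour of** acupuncture.
- Slowest three lost from the sham arm (SD 4.31): 0.294 × 4.31 = 1.27 h faster, 1.27 / 4 = 32% of the target, **against** acupuncture.

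The −0.296 figure gives 0.855 h and 1.275 h, the same percentages. The two shifts have opposite signs and should not be read as one range.

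**4. Effect on the type I error.** Simulated with no true effect, removing only the slowest acupuncture subjects and leaving sham at 17:

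| Removed | Common SD 3.67 h | SDs 2.89 h and 4.31 h |
|---|---|---|
| 0 | 5% | 5% |
| 1 | 7% | 6% |
| 2 | 11% | 8% |
| 3 | 15% | 10% |

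The common SD is √((2.89² + 4.31²) / 2) = 3.67 h.

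**5. Power if everyone is kept.** For a two-sided t test with difference 4 h and SD 3.67 h, the noncentrality is 4 / (3.67 × √(2/n)).

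- n = 14: noncentrality 2.88, power 0.793 (normal approximation 0.822).
- n = 17: noncentrality 3.18, power 0.869 (normal approximation 0.888).

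The second line assumes that all 17 flatus times are observed.

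**The case against.** The strongest reply is that the article intends both analyses. It commits the data to intention-to-treat, and Analysis procedures speaks of describing the size and dropout rate of each dataset, which suggests more than one set. That reading is open. It means the document does not show that intention-to-treat has been abandoned or that completers are the only population. It does not rescue the wording, because even then no set is primary and the sentence on efficacy and safety names only per-protocol.

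Other stronger readings also go further than the text:

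- **One missed visit removes a subject.** The follow-up criterion concerns inability to attend the follow-ups, whatever the reason. It does not say that a single absence is enough. That a missed one-month visit costs a recorded flatus time is a plausible inference from the completer definition, not a stated rule.
- **Harms go unrecorded.** They do not. Safety indicators requires detailed records whether or not events are related to treatment, and reporting of serious events to the review board. Analysis procedures lists events with severity and cause and gives dropout reasons. The valid point is narrower: the comparison is confined to completers.
- **Conversion to laparotomy biases the comparison.** Under Randomization, envelopes are opened only after all baseline evaluations, and the Intervention section puts the first evaluation 6 h after surgery. Conversion therefore probably comes before the arm is known. It costs numbers but is not shown to cause bias.
- **The arms will lose subjects differently.** Pressed needles against tape makes this possible. However, the article caps pressing by a pain score and reports strict adherence in its six-subject pilot. Differential loss is undocumented.

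**Conclusion.** The point holds in this form: the printed rule contradicts the intention-to-treat commitment and names no primary population. Read with the elimination list, it points efficacy and safety to a selected set. The safety consequence is the most serious, since coma, death and serious complications are themselves reasons for removal.

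The size is a bound on what exclusion alone could do, not a forecast: about 0.85 h towards acupuncture or about 1.27 h away from it, against a 4 h target. It rests on normality, SDs from a six-subject pilot, three losses in one arm, and those three being the slowest. The documents give neither the number nor the pattern of eliminations. The sample size calculation itself is not at fault.

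**What to change.** In Statistical analysis methods, state that:

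- the primary efficacy analysis includes all randomised subjects as allocated and uses every recorded flatus time;
- the per-protocol analysis is a sensitivity analysis only;
- safety is analysed in all subjects who received at least one session, by treatment received.

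In Elimination criteria, recast the post-randomisation reasons as events to be recorded, with data already collected kept and outcome follow-up continued where possible.

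This needs no extra subjects, and no change to when sequence numbers are issued. The cost is that non-compliant subjects stay in the primary analysis, so the estimate may be slightly less favourable. Against that, power for 4 h rises from about 79% with 14 per arm to about 87% if all 17 flatus times are available. Recruitment is ongoing, so the wording should be settled before anyone sees results by arm.

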## Discussion

Since postoperative gastrointestinal dysfunction seriously affects prognosis after abdominal surgery, clinicians and researchers must find treatments that promote early recovery of gastrointestinal function. Acupuncture is an important component of traditional Chinese medicine. It is technically simple to perform and easy to teach. Some research has indicated that acupuncture promotes postoperative recovery of gastrointestinal function [25, 26]. However, few high-quality studies support the technique in this regard. Therefore, to improve treatment, we conceived of the clinical method used in the pilot trial. In the proposed study, we will use XNKQAT intradermal needling to treat gastrointestinal dysfunction after laparoscopic surgery. Furthermore, since the time until the first postoperative flatus has clinical significance in postoperative recovery of gastrointestinal function [27], we will use it as the primary outcome in the trial.

A lot of studies have focused on acupuncture, its therapeutic effects, and its procedures, which are based on thousands of years of empirical practice. Furthermore, acupuncture is now used worldwide to treat diseases, and many studies have applied advanced molecular biology methods to study acupuncture. However, since traditional Chinese medicine is based on a different philosophy from translational medicine, it is difficult to incorporate acupuncture into treatment regimens. Nevertheless, recent advances in neuroendocrinology and immunology have allowed a better understanding of acupuncture. From a translational medicine perspective, we herein present a clinical trial protocol that adheres to scientific standards to evaluate the safety and efficacy of XNKQAT in the treatment of postoperative gastrointestinal dysfunction. The results of the trial will determine whether this treatment should be more widely applied in clinical practice. In addition, we intend to use this work to emphasize that the effects of acupoint stimulation on the human endocrine system must be mapped; this will enable further integration of acupuncture into current scientific practice. Herein, we present a promising new approach to the fusion of acupuncture and mainstream medicine, and we use XNKQAT as an example.

### Trial status

Recruitment for this trial is currently ongoing.

